#### Formal Carers: Aged Care Service Providers

The outcomes collected from the respective aged care service providers at the end of the trial are shown in Table 4.

**Table 4 table4:** Data collected from aged care providers.

Outcome/objective	Data variable	Data source
Impact of care: case manager	Four-level self-completion questionnaire with eight attributes: control over daily life, personal cleanliness and comfort, food and drink, personal safety, social participation and involvement, occupation, accommodation cleanliness and comfort, dignity. Additional questions: subjective rating of health, open question	ACCOM^a^ measure (adapted from ASCOT^b^ for the Australian population)
Organizational change management and impact on workplace culture	Administrative/operational changes implemented/required to implement the SSH^c^ service	Semistructured interviews during focus groups with the formal carers
User perceptions of the SSH system	Ease of use, quality of training received, easy or hard to take and monitor clients’ measurement. Responsiveness of Project Officer to changes in O-ADLs^d^, effectiveness in improving ability to deliver care, impact on workload	Semistructured interviews during focus groups with the formal carers

^a^ACCOM: Australian Community Care Outcome Measurement.

^b^ASCOT: Adult Social Care Outcome Toolkit.

^c^SSH: Smarter Safer Homes.

^d^O-ADL: Objective Activities of Daily Living.

#### Government Data Source

The outcomes collected from the Commonwealth Government Department of Health (Services Australia) and the QLD Government Department of Health (hospital data custodians) at the end of the trial are shown in Table 5.

**Table 5 table5:** Data collected at the administrator level.

Outcome/objective	Data variable	Data source
Hospitalization	Admitted hospital separations (same day or overnight) and emergency department presentations	Queensland Hospital admitted patient data collection (Queensland Health Statistical Services Branch), emergency department collection (Healthcare Improvement Unit)
Use of clinical services	Nonreferred (eg, general practitioner) attendances, attendances to specialists, allied health professionals, pathology (hematology, etc), diagnostic imaging (X-ray, etc)	Medicare benefits schedule claims, Services Australia
Pharmaceutical Benefits Scheme (PBS) expenditure	Prescription medications	PBS claims, Services Australia

### Data Management

Data were predominantly captured in the ethics-approved and secure REDCap system. All survey responses were collected through REDCap with the exception of interviews that were captured through recordings. Health services utilization data, already captured through business-as-usual processes of the relevant health services, were utilized in the analysis. Every participant was allocated a REDCap identifier. Once allocated, REDCap numbers were the only identifier of research participants. Interviews with aged care service providers were performed one-on-one with participants and therefore the interviewees were identifiable to the interviewer. 

### Statistical Methods

#### Data Collection and Missing Data

Survey results were collected at three time points: at the baseline, middle, and end of the study. The final survey data included in our analyses contain results from participants with a baseline survey and at least one follow-up and middle/end survey. For missing responses in surveys, we will conduct a case-by-case retrospective analysis with project officers and aged care service providers, and/or use multiple imputation methods to replace missing data.

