## Methods

### Trial Design

The trial was designed as a single-blind, stratified RTC. Participants were divided into two groups with an allocation ratio of 1:1. Trial participants could not be blinded as the intervention required physical installation of equipment in their homes. Researchers undertaking data analyses are blinded to which participants received the intervention. Access to community health services has previously been identified to vary by geographic location [24]. To ensure balance between the intervention and control groups relative to this potential confounder, stratification based on region (ie, metropolitan or regional area) is used.

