#### Primary Outcome

The primary outcome was the Australian Community Care Outcome Measurement tool (ACCOM) [27].

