#### SSH Kit Installation

Once participants had been consented, a set of surveys was administered by the project officer. The participants allocated to the intervention group received an SSH kit. Installation of the SSH kit (tablet, hub, sensors) was coordinated by the project officer, typically within 2 weeks of consent and randomization. A user sheet that describes how to interact with the tablet and interpret the information presented on the tablet SSH app was included with the kit. The project officer also demonstrated to the participant how to use the tablet and the SSH app during installation. To obtain valid baseline data after installation, the SSH system gathered 14 days of the participants’ normal living routines in their homes. After the baseline data had been gathered, the identified aged care service providers and the nominated family portal users were notified of their user ID, password, and access instructions. During the trial period, the project officer was the point of contact for any problems or questions. Technical issues that were not easily addressable were escalated to the research technical team who worked to find efficient and effective solutions. All reported issues, no matter how minor, were reported to the project manager for inclusion in the monthly project reports. If a participant wished to withdraw from the trial, the project officer arranged for an uninstall to occur as quickly as possible from the home. Upon completion of the project, all homes had their trial equipment removed by the project officer. Participants allocated to the usual care group continued to receive their existing care and social services in line with local aged care service provider protocols for the 12 months of the trial. They did not have any SSH equipment installed in their homes.

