#### Survey Questionnaires

##### Baseline

The project officers administered a baseline survey to all consented participants. Questionnaires included in the baseline survey are listed in Table 2. Note that the Abbreviated Mental Test Score (AMTS) was administered by a project officer prior to administering the baseline survey. Follow-up questionnaires at the mid-trial point (around 6 months) and end-trial point (around 12 months) included the same battery of questionnaires except for the demographics and AMTS. The baseline survey was delivered to participants during the consent face-to-face meeting and took approximately 45 minutes to complete.

**Table 2 table2:** Survey questionnaires.

Domain	Measure	Context	Score meaning/presentation	Time point		
				Start	Mid	End
Demographic information	Individual questions	Gender, age, weight and height (BMI), occupation, marital status, income, computer skills, social media, and NBN^a^ connectivity	Individual and coded scores	✓		
Cognitive level	Abbreviated Mental Test Score (AMTS) [35]	To establish baseline cognition (10 questions)	Maximum score 10; a score of less than 7 or 8 suggests cognitive impairment	✓		
Impact of care: participant	ACCOM^b^ measure (adapted from ASCOT^c^ for the Australian population) [33]	Self-completion (eight attributes): control over daily life, personal cleanliness and comfort, food and drink, personal safety, social participation and involvement, occupation, accommodation cleanliness and comfort, dignity. Additional questions: subjective rating of health, open question	Four levels: Ideal State, No needs, Some needs, High needs; ASCOT scoring [36]	✓	✓	✓
Health-related quality of life	EQ5D^d^ [37]	Five generic questions on health status: mobility, self-care, usual activities, pain/discomfort, anxiety/depression; respondents’ self-rated health is recorded on a vertical, visual analog scale (VAS: 0-100)	Results presented as an index value (Australian Scoring algorithm); VAS presented as a number from 0 to 100, with 0 indicating the worst and 100 indicating the best imaginable health state	✓	✓	✓
Activities of Daily Living (ADL)	Katz’s ADL [29]	Assesses basic ADLs: feeding, continence, transferring, toileting, dressing, bathing	Maximum score of 6 points indicating fully independent, 4 points indicating moderately impaired, and 2 points indicating severely impaired	✓	✓	✓

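### The missing-data rule does not bar project officers and providers, who know the arm, from supplying values for the participant-completed ACCOM and other participant-reported outcomes

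*Protocol article*

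**What the plan says.** Under Data Collection and Missing Data, the protocol article says that for missing survey responses "we will conduct a case-by-case retrospective analysis with project officers and aged care service providers, and/or use multiple imputation methods to replace missing data". No rule says which route applies to which participant, and no outcome is exempt.

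The primary outcome is ACCOM. Table 2 describes the participant version as "Self-completion (eight attributes): control over daily life, personal cleanliness and comfort, food and drink", and so on through dignity. Table 4 lists a provider-rated version separately, as "Impact of care: case manager".

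On who knows the allocation:
- Trial Design states that participants could not be blinded and that "Researchers undertaking data analyses are blinded to which participants received the intervention". No other blinding is described.
- SSH Kit Installation says "Installation of the SSH kit (tablet, hub, sensors) was coordinated by the project officer". The officer also demonstrated the app, and providers were then given portal access. Control homes had no SSH equipment.
- The Intervention section has providers monitoring clients through the portal and responding to red flags.

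**The concern.** ACCOM records how the participant rates matters such as control over daily life, safety and dignity. The rule leaves room for someone else to fill a gap in that record after allocation is known. The people named know the arm. Providers also hold portal information on one arm only, so what they could contribute differs systematically between arms.

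A value set this way enters the dataset before the blinded analyst sees it, so analyst blinding is bypassed. Once merged into the scores, such values can no longer be told apart unless they were flagged.

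The opportunity is real. The analysis set admits participants with a baseline survey and only one follow-up, so a whole 6- or 12-month survey can be missing. The Friedman test needs all three surveys.

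**Working it through.** **Does the text allow it?** Three statements, side by side:
1. Missing-data rule: retrospective work with officers and providers, *and/or* multiple imputation, with the purpose of replacing missing data. *And/or* permits the first route alone.
2. Table 2: the primary outcome is self-completed.
3. SSH Kit Installation and Intervention: officers and providers know the arm from their roles. No section calls them unblinded in so many words, but it follows from what they do.

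Taken together, values from staff who know the arm are not excluded from the primary outcome.

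**Inputs from the documents.** Target difference 0.08, SD 0.16, 1:1 allocation, 134 evaluable, 30% attrition, 195 recruited (98 and 97 in the abstract).

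**The plan's own figure.** With standardised effect 0.08/0.16 = 0.5, two-sided alpha 0.05 (sidedness is not stated and is assumed) and 80% power, a t-test needs 63.77 per arm. Dividing by the rank-sum efficiency under normality, 3/π = 0.955, gives 66.78, so 67 per arm and 134 in total. The stated figure is reproduced. It is not in dispute and only confirms the inputs.

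**Standard error.** 70% of 195 is 136.5, so take 136 analysed. SE = 0.16 × 2/√136 = 0.0274.

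**Formulas.** With no true effect, bias = (fraction filled) × (between-arm shift in the filled values). Type I error = P(|Z + bias/SE| > 1.96), a normal approximation to a comparison of means.

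**Assumptions not in the documents.** Fraction filled 10% or 20%; shift 0.08 to 0.10; in the item-level case, eight equally weighted items.

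| Case | Bias | Share of 0.08 | Bias/SE | Type I error |
|---|---|---|---|---|
| 20% of whole scores, shift 0.08 | 0.20 × 0.08 = 0.016 | 20% | 0.58 | 9.0% |
| 20% of whole scores, shift 0.10 | 0.20 × 0.10 = 0.020 | 25% | 0.73 | 11.3% |
| 10% of whole scores, shift 0.08 | 0.008 | 10% | 0.29 | 6.0% |
| 10% of whole scores, shift 0.10 | 0.010 | 12.5% | 0.36 | 6.5% |
| One of eight items in 20%, shift 0.08 | 0.20 × 0.08/8 = 0.002 | 2.5% | 0.07 | 5.1% |
| One of eight items in 20%, shift 0.10 | 0.20 × 0.10/8 = 0.0025 | 3.1% | 0.09 | 5.1% |

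**Sensitivity.** With all 195 analysed, SE = 0.16 × √(1/98 + 1/97) = 0.0229, and a bias of 0.016 gives 10.7%. Widening the assumptions to 5% to 30% filled and a shift of 0.04 to 0.16 gives bias from 0.002 to 0.048 and type I error from 5.1% to 55%. The documents do not narrow that range.

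**The case against.** The strongest reply is grammatical. The phrase about replacing missing data may belong to multiple imputation alone. The work with staff would then be a query: why is the answer missing, was there an entry error, did the participant withdraw? Project officers administered the surveys, so they are the natural people to ask. This reading is possible, and a reader should not infer that the protocol says staff will supply values. What stands against it is that the sentence fits either reading, and the primary outcome is at stake.

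Other stronger readings also go beyond the documents:
- *The bias favours the intervention.* Providers are project partners, which might suggest this. But the portal also shows them amber and red warnings for intervention clients, which could lower their ratings. No direction is documented.
- *Analyst blinding is defeated.* Analysts can stay unaware of allocation. The blinding simply does not reach values set earlier by others.
- *Standard errors would be too small because single values are filled in.* No fill-in procedure is described, so this cannot be asserted.
- *Type I error is about 9% to 11%.* That holds only if whole scores are filled at the assumed rate. The text speaks of missing responses, which may mean single items, and then the effect is close to nil.

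It is also fair to say that some input from people who know the arm is already present: participants are unblinded, and the officers who coordinate installation also contact participants for the follow-up surveys. That does not justify substituting a third party's answer.

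**Conclusion.** The point holds as a defect in a stated rule. The text does not exclude values from staff who know the arm in a self-completed primary outcome or in the other participant-reported outcomes, and it leaves the choice of route open for each case. That staff knew the arm follows from their documented roles.

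The size cannot be fixed from the documents. It runs from negligible (bias about 0.002, type I error about 5.1%) if isolated items are filled, to a fifth or a quarter of the target difference (type I error about 9% to 11%) if 20% of whole scores are filled with a shift of 0.08 to 0.10. The direction is unknown. The case for correcting the rule does not depend on where in that range the truth lies, because the safeguard is cheap and the plan already names the alternative method.

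**What to change.** Reword the missing-data sentence to say that:
- contact with project officers and providers serves only to establish why a response is missing or to correct a recording error against source, and never to supply a participant-reported value;
- multiple imputation replaces *and/or* as the single method for missing scores, using baseline and other-visit scores, arm and region;
- the case-manager ACCOM in Table 4 remains a separate outcome and does not stand in for the participant's score.

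The cost is a changed sentence and modest imputation code. No new data are needed and no sample-size figure changes. A few more responses stay missing and are imputed. The article describes the final analysis as still underway, so the wording should be settled before any values are merged; any already supplied by staff should be identified and set back to missing. A delta-adjusted sensitivity analysis would be a useful option but is not needed to cure this defect, and neither is a different longitudinal model.

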#### Survey Data Analyses

At each survey time point, intergroup differences in survey results between the intervention and control groups will be analyzed by *χ*^2^ tests and Wilcoxon rank-sum tests. If significant differences in survey results are observed, a log-binomial regression model will be further used to estimate the relative risk of each group to changes of survey results. Within each group, for all three surveys, the Friedman nonparametric test will be used to understand intragroup differences in survey results. Similarly, if significant differences in survey results are observed, the Wilcoxon signed-rank test with Bonferroni correction will be used to further investigate pairwise differences between surveys.

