#### Secondary Outcomes

The secondary outcomes included change in health-related quality of Life, as measured by the Five-Dimension EuroQuol (EQ5D 5-L) questionnaire [28]; Katz ADL [29] and instrumental ADL (Lawton iADL [30]); depression (Geriatric Depression Scale [31]); health service utilization, including community prescription medicines (collected based on Pharmaceutical Benefit Scheme [PBS] claims data), community health services (including nonreferred medical attendances such as general practitioner appointments, attendances with medical specialists, pathology, diagnostic imaging, and Allied Health attendances collected from Medical Benefit Scheme [MBS] claims data), hospital attendances (same day and overnight admitted), and emergency department presentations (collected from QLD public hospital data); changes in service design, adoption, and aged care service provider experiences (based on provider staff interviews); care giver burden (Zarit Burden Interview [ZBI]-12 [32]); and costs to deliver the SSH supported care.

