### Sample Size

The primary outcome of this trial, the impact of community care for older people, will be evaluated using the ACCOM tool [27], a set of measures of community care suitable for use in the Australian context. The ACCOM mainly uses questions from the Adult Social Care Outcome Toolkit (ASCOT) [33], which is a validated measure of social care related to quality of life. Power was based on a randomized trial design with a clinically important difference of 10% on the primary outcome of ASCOT with a mean 0.80 (SD 0.16) distribution (ie, 0.08, based on previous research [33]). With the threshold of rejecting the null hypothesis of *α*≥.05, effect size of 0.5 (0.08/0.16), and the same allocation ratio of the two groups in our trial. Figure 3 illustrates the relations between total sample size and statistical power.

To achieve 80% statistical power, we needed a total of 134 participants. Allowing for a 30% attrition rate, the sample size of this trial was computed to be 200 participants. We did not anticipate an attrition rate greater than 30% as all participants were existing clients of the participating aged care service providers and received regular visits throughout the trial period. The intervention and outcome measurement collection processes were designed to minimize participant burden. In addition, the power analysis did not consider the repeated-measures design of the trial. Repeated measures increase the power of the trial to find a significant result and appropriate statistical techniques will be applied to ensure that all data available are used in the analyses.

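### The between-arm ACCOM tests, unadjusted and run visit by visit, cannot deliver the extra repeated-measures power and full use of the data that the sample-size section promises

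*Protocol article*

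**What the plan says.** The Sample Size section states that the power calculation left the repeated-measures design out of account. It continues: "Repeated measures increase the power of the trial to find a significant result and appropriate statistical techniques will be applied", with the aim that all available data enter the analyses.

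The Survey Data Analyses section sets the between-arm comparison: "At each survey time point, intergroup differences in survey results between the intervention and control groups will be analyzed by" chi-square and Wilcoxon rank-sum tests. If a test is significant, a log-binomial regression follows to estimate a relative risk; no covariates are named. The Friedman test and the Bonferroni-corrected signed-rank tests use all three surveys, but within each arm.

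On region, the Trial Design section says: "To ensure balance between the intervention and control groups relative to this potential confounder, stratification based on region" was used. No survey analysis mentions region again. Table 2 has ACCOM collected at start, mid-trial and end, and the Allocation section places the baseline survey before randomisation. The Secondary Outcomes section words one outcome as a change: "The secondary outcomes included change in health-related quality of Life". Adjustment for baseline differences appears only for costs, in the cost-effectiveness section.

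**The concern.** The promise and the method do not match. A gain from repeated measures can reach the treatment effect only through a between-arm analysis that uses a person's own baseline, or several follow-ups, or both. The written tests do neither, and the methods that do link visits give no contrast between arms.

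At stake is precision on the primary outcome. Baseline ACCOM is recorded before allocation and is likely to predict follow-up ACCOM. Leaving it out keeps explainable variation in the error, and any chance baseline difference stays in the observed treatment difference. In addition, the plan yields an effect estimate only after a significant test, and then as a relative risk, although the trial was sized on a mean difference.

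**Working it through.** **Inputs (Sample Size section).** The design assumes a "clinically important difference of 10% on the primary outcome of ASCOT with a mean 0.80 (SD 0.16) distribution". The difference is therefore 0.10 × 0.80 = 0.08, and d = 0.08/0.16 = 0.5. Power is 80%, 134 evaluable, 30% attrition, 200 planned, 1:1 allocation. The Results section reports 195 recruited. Sidedness is not stated; two-sided 5% is assumed and reproduces the plan's number.

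**Step 1: reproduce 134.** For normal data the rank-sum test has efficiency 3/π = 0.955 relative to the t-test.
- Effective n per arm = 67 × 0.955 = 63.98.
- Noncentrality = 0.5 × √(63.98/2) = 2.828.
- Power = 80.1%.

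So 67 per arm, 134 in total, is the rank-sum sample size at a single visit. A t-test would need 64 per arm (128).

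**Step 2: power as recruited.** 195 × 0.70 = 136.5, or 68 per arm. Rank-sum power is 80.7%.

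**Step 3: adjust for baseline at 12 months.** Residual variance is multiplied by 1 − r², so the working effect size is 0.5/√(1 − r²). The correlation r between baseline and 12 months is not in the article; 0.3 to 0.7 is an assumption. Normal errors, 68 per arm:

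| r | 1 − r² | Fall in residual variance | Effect size | Power |
|---|---|---|---|---|
| 0.3 | 0.91 | 9% | 0.524 | 85.9% |
| 0.4 | 0.84 | 16% | 0.546 | 88.5% |
| 0.5 | 0.75 | 25% | 0.577 | 91.7% |
| 0.6 | 0.64 | 36% | 0.625 | 95.1% |
| 0.7 | 0.51 | 49% | 0.700 | 98.2% |

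**Step 4: use both follow-ups.** If the effect is the same at 6 and 12 months and all visit pairs share the correlation r, the variance factor for the mean of the two is (1 + r)/2 − r²: 0.56, 0.50 and 0.36 for r = 0.3, 0.5 and 0.7. Power at 67 per arm is then about 97%, 98% and above 99%. These figures rest on the constant-effect assumption as well as on r.

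**Step 5: drop normality.** A mean of 0.80 with SD 0.16 on a 0–1 score (assumed bounds) leaves (1 − 0.80)/0.16 = 1.25 SD of headroom. Simulated power with left-skewed Beta scores, a difference of 0.08 and 68 per arm:

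| Scenario | Rank-sum | Mean-based ANCOVA, r = 0.3 / 0.5 / 0.7 |
|---|---|---|
| Intervention mean 0.88, SD 0.16 | 98–99% | 84 / 89 / 97% |
| Intervention mean 0.88, SD 0.12 | about 92% | 93 / 96 / above 99% |
| Lower arm mean 0.72, SD 0.16 | about 90% | 85 / 91 / 98% |

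The mean-based model can therefore do worse than the plain rank-sum test: clearly at low r, and in the first scenario slightly even at r = 0.7. A baseline-adjusted rank analysis had more power than the plain rank-sum test in every case run.

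**The case against.** The strongest reply is that nothing the plan relies on breaks. The sample size was computed without repeated measures, it matches the planned test, and that test is valid at a given visit. This stands. A reader might infer that the trial is underpowered; Steps 1 and 2 show that it is not at the planned attrition. Nor does the article support arguing from heavier loss, since it expects no more than 30%.

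A reader might also infer bias. Under randomisation, an omitted baseline score costs precision and does not bias the comparison. Omitting the stratum usually makes the test slightly conservative, by an amount that the article does not allow one to compute.

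It would also go too far to say that someone with only a 6-month survey contributes nothing at 12 months. The missing-data section keeps anyone with a baseline and one follow-up survey and allows multiple imputation. That imputation is optional, however, and adds neither the baseline score nor a second visit to the between-arm test. The log-binomial step does refer to changes in results, but it runs only after significance and needs a binary outcome.

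Finally, bounded or coarse scores make rank methods defensible, and Step 5 bears this out. It argues for keeping a rank analysis, not for leaving baseline out.

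One could reply that covariates belong in an analysis plan that is not shown. But the article does name its tests, and the point is that they conflict with its own sample-size section.

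**Conclusion.** The conflict is real and concerns the primary comparison, but it is a loss of efficiency and not a failure of the design. The 80% target holds. The additional power does not exist under the written tests. Its size depends on assumptions: roughly 5 to 17 percentage points at 12 months (85.9 − 80.7 to 98.2 − 80.7) for r of 0.3 to 0.7 with normal errors. With a skewed, bounded score the gain from a mean-based model is smaller and can be negative. The case for using baseline is firmer than the case for any one model. Severity: should be fixed.

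**What to change.** In a dated amendment made before unblinding, define the primary ACCOM comparison as one baseline-adjusted between-arm longitudinal analysis over 6 and 12 months. An example is a mixed model with arm, visit, arm-by-visit, baseline ACCOM and region, with robust standard errors. Report the adjusted 12-month difference with its 95% CI whether or not it is significant.

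Keep a rank analysis, stratified by region and preferably baseline-adjusted, as a prespecified sensitivity analysis for skew or ceiling. For the secondary scores, adjust for baseline and region by a method suited to each scale; one Gaussian model for Katz, Lawton, the depression scale and the carer-burden score would overreach.

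No new data are needed. The cost is a rewritten analysis section, some code, a mean-based primary model on a bounded score, and a documented amendment. Timing matters: the Results section says that final analysis is underway, while the Trial Design section says that analysts are blinded to allocation, so the amendment should record that it was made blind.

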### Outcomes

#### Baseline Characteristics

Baseline characteristics were collected to facilitate the identification of systematic differences between study groups that may increase the risk of bias.

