### Assignment of Intervention

#### Allocation

Stratified randomization was used with the strata defined by geographical areas (ie, metropolitan and regional). Within each area, simple randomization (ie, randomization based on a single sequence of random assignments [34]) was performed and participants were assigned to either the provider’s usual care or their services designed and delivered through the SSH technology platform (smart home group). Randomization of participants was undertaken using a computer program and carried out by an independent researcher using anonymized identifiers. The random allocation sequence was delivered through the REDCap application. Allocation occurred after the baseline survey had been completed.

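### The survey plan tests the arms against each other at baseline, before allocation, and its trigger permits a chance baseline difference to start the effect model

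*Protocol article*

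**What the plan says.** Four statements in the protocol article bear on this.

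- Data Collection and Missing Data lists the surveys: "Survey results were collected at three time points: at the baseline, middle, and end of the study". The same section restricts the survey data to a set that will "contain results from participants with a baseline survey and at least one follow-up and middle/end survey".
- Survey Data Analyses sets the between-arm tests: "At each survey time point, intergroup differences in survey results between the intervention and control groups will be analyzed by" chi-square and Wilcoxon rank-sum tests. No time point is excepted.
- The next sentence sets the trigger: "If significant differences in survey results are observed, a log-binomial regression model will be further used to estimate the relative risk of each group". The target of that model is to "estimate the relative risk of each group to changes of survey results".
- Allocation fixes the order of events: "Allocation occurred after the baseline survey had been completed".

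Survey Data Analyses names no adjustment for the baseline score. The only baseline adjustment in the article is for the cost comparison, in the cost-effectiveness section.

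**The concern.** A between-arm test at baseline asks whether groups formed by randomisation differ on data collected before they were formed. For all randomised participants the answer is known: any gap is chance. For the analysed set the question is less clean, because having a follow-up survey is a selection made after randomisation and dropout may differ by arm. Either way, the p-value says nothing about the platform and does not say which cause is at work.

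The trigger adds a second problem. Taken literally, a significant baseline result is enough to start a model of relative risk for change. There is no change at baseline to model. If the model is then run on later change, an arm that started high by chance will tend to fall and an arm that started low will tend to rise. Regression to the mean can then look like a group effect.

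**Working it through.** **The plan's own figure.** The article gives no figure for the baseline tests. Its sample size can be reproduced and shows which test was in mind. With effect size 0.5 (0.08/0.16), two-sided alpha 0.05 (sidedness is not stated and is assumed) and 80% power, the t-test needs 63.77 per arm. Dividing by the rank-sum efficiency 3/π gives 66.78, so 67 per arm and 134 in total, which is the stated number. The calculation involves no baseline test, so removing that test leaves the sample size unchanged.

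**Does the rule reach baseline?** There are three survey time points and baseline is the first. The arms are tested at each of them. The baseline survey precedes allocation. So the testing of baseline data between arms is explicit. The trigger sentence speaks of significant differences in survey results and is not limited to follow-up, so a baseline trigger is permitted.

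**Chance of a spurious baseline result.** Table 2 lists five participant instruments at the start: ACCOM, EQ-5D, Katz ADL, Lawton iADL and the Geriatric Depression Scale. If the EQ-5D index and its visual analogue scale are counted separately there are six scores. With one test per score at 0.05 and correct randomisation, the chance of at least one p<0.05 under independence is 1 − 0.95^k:

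- k = 5: 1 − 0.95^5 = 0.226
- k = 6: 1 − 0.95^6 = 0.265

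These are upper values, because the scores are probably positively correlated. For six scores, simulation with assumed pairwise correlations of 0.3 and 0.5 gives 24.1% and 20.7%. Carer burden is left out: it is not in Table 2, it goes to carers by post or email, and the article does not say whether the carers' first survey preceded allocation.

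**False-positive rate of a change model started by a chance baseline gap.** The document does not give the correlation r between baseline and follow-up scores, so 0.3 to 0.7 is assumed. Let Zb and Zf be the between-arm test statistics at baseline and follow-up, with equal variances, correlation r and no intervention effect. The statistic for change is

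Zc = (Zf − Zb) / √(2(1 − r)), with corr(Zc, Zb) = −√((1 − r)/2).

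The probability that |Zc| > 1.96 given |Zb| > 1.96, from the bivariate normal, is:

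| r | corr(Zc, Zb) | False-positive rate |
|---|---|---|
| 0.3 | −0.59 | 24% |
| 0.5 | −0.50 | 19% |
| 0.7 | −0.39 | 13% |

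The nominal rate is 5%. This treats change as a continuous score. The article does not say how change would be made binary for the log-binomial model, so these figures show direction and rough size.

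**Effect of removing the baseline test.** For each outcome, the number of between-arm tests that can start the model falls from three to two. If the tests are independent, the null chance of a trigger falls from 1 − 0.95^3 = 14.3% to 1 − 0.95^2 = 9.75%. In simulation (98 v 97, correlations 0.3 to 0.7) it falls from 13.5%–11.3% to 9.3%–8.5%. The chance of a trigger from the baseline test itself falls from 5% per outcome to zero.

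**The case against.** The strongest reply is that the log-binomial step concerns change. No change exists at baseline, so the authors probably meant follow-up results only. This stands in part. A reader might infer that the plan intends to report a relative risk for the period before installation, but the document does not support that. It supports only that the wording permits a baseline trigger. The baseline testing itself does not depend on this reading.

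A second reply is that a baseline gap need not be chance, because the analysed set is selected by follow-up and the sample size allows for 30% attrition. This also stands, so it would be wrong to call every baseline gap chance by construction. For the same reason the Baseline Characteristics sentence, "Baseline characteristics were collected to facilitate the identification of systematic differences between study groups that may increase the risk of bias", is not an error. It prescribes no test, and differential dropout is a systematic difference worth looking for. Comparing descriptive tables for the randomised and the analysed participants would show it better than a p-value.

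A third reply is that larger harms could be claimed and would not hold. One might test all eight ACCOM attributes and get a spurious result about a third of the time, but that needs assumed response shares, an assumed correlation and a testing scheme that the article does not state. One might also note that a baseline gap just short of significance distorts an unadjusted follow-up test. At 1.9 standard errors and an assumed correlation of 0.6, its conditional error is about 15%. That comes from not adjusting for baseline, and deleting the baseline test does not cure it. Averaged over all non-significant baseline results, the follow-up false-positive rate is below nominal (4.3% at r = 0.5).

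Finally, no 6- or 12-month test is made conditional on a baseline result. This stands and sets the severity.

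**Conclusion.** The point holds as a minor fault in a stated rule. The plan tests the arms against each other on data that precede allocation, and its trigger does not exclude that result from starting the effect model. The chance of at least one spurious baseline finding is at most about 23% for five instruments or 26% for six scores, given one test per score at 0.05 and no negative dependence between scores. If the trigger were used at baseline, the false-positive rate of a change analysis would be roughly 13% to 24%. That range rests on assumed correlations of 0.7 to 0.3 and on treating change as continuous. The 6- and 12-month tests and the sample size are unaffected.

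**What to change.** In Survey Data Analyses, begin the first sentence with *At the 6-month and 12-month surveys* in place of the reference to every time point. State that the log-binomial step uses follow-up results only.

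Present baseline scores by arm as summary statistics without p-values, once for all randomised participants and once for those analysed, so that chance imbalance and differential dropout can be told apart as far as the data allow.

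State that the follow-up between-arm comparisons are adjusted for the baseline score whatever the size of any baseline difference. The rank-sum and chi-square tests do not do this, so an adjusted model has to be named.

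Leave the Baseline Characteristics sentence as it is.

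The cost is a few sentences and one adjusted model per outcome. No new data are needed, and the baseline scores are already collected. The Results section says that final analysis was still under way, so when the article was written the rule could still be changed.
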